### Qualitative interviews

Qualitative interviews are conducted on an individual basis at the end of the 12-week treatment period. The interviews are semi-structured with open-ended questions, asking how patients feel about the treatment they received, whether it meets their expectations, and what they like and dislike. Participants are also asked to identify the factors they consider when determining their satisfaction with care and which outcome measures they consider most important.

### Data analysis

#### Treatment effect

Power was calculated to detect a medium effect size difference in the primary outcome measure of patient self-report pain. A sample size of 240 subjects per study is needed to provide 88% power to detect a difference of eight percentage points between the highest and lowest group means, assuming and alpha level of 0.05. This allows for a 15% drop out or loss to follow-up rate.

Primary analysis will use repeated measures analysis of covariance (ANCOVA) to measure differences between the 3 groups in patient-rated pain using weeks 4 and 12 data for the short-term outcome, and weeks 4, 12, 26, and 52 for the long-term outcome. Baseline values will be used as covariates, and 95% confidence intervals will be placed on group differences. Possible treatment-time interactions will be accounted for and an intention-to-treat analysis will be used [50]. A confirmatory, secondary analysis using a repeated measures, multivariate analysis of covariance (MANCOVA) will be used as an overall test for differences between groups. This will include both the primary and the secondary patient-rated outcomes to assess short- and long-term efficacy.

#### Cost-effectiveness analysis

A cost comparison of the intervention and control groups will be performed using data on direct and indirect costs. Cost differences between groups will be estimated using regression analysis where all neck or back-related costs in a year are regressed on treatment. A cost-effectiveness analysis, using a mixed-model linear regression analysis, will be conducted to compare the interventions with home exercise (as the control), using patient-rated pain as the effectiveness measure. Finally, a cost-utility analysis comparing the intervention and control groups will be performed using the EuroQol-5D.

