### Randomization

Restricted randomization with a 1:1:1 allocation ratio has been applied using randomly permuted block sizes. The randomization scheme and block sizes are concealed from the study team to ensure they are masked to the sequence of treatment assignments. As individuals become eligible, sequentially numbered opaque envelopes with treatment assignments are drawn.

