### Health care costs/cost utility analysis

Direct costs for each patient will represent the one-year aggregated LBP or NP related health care costs based on utilization and estimated costs. Health care utilization (within and outside of the studies) is measured using standardized clinician treatment forms (each visit, weeks 1 to 12), monthly phone call interviews (weeks 16 to 52) and patient self-report questionnaires (baseline and weeks 4, 12, 26 and 52). Direct health care costs include costs related to study treatment, non-study health care health provider use, medication utilization, and hospitalizations for LBP or NP. Indirect costs of wage and productivity loss are measured through patient self-report (weeks 4, 12, 26, and 52) using three questions from the National Health Interview Survey (NHIS) that measure lost or impacted work or activity days due to back or neck pain [47]. The EuroQol 5D, a multi-attribute, patient self-report utility scale measuring five dimensions (mobility, self-care, usual activities, pain/discomfort, and anxiety/depression), is used as the cost-utility index [48,49]. It is measured at baseline and weeks 4, 12, 26, and 52.

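### The one-year cost regression names no baseline covariate although baseline utilization is collected: a small, avoidable loss of precision, not a bias

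*Protocol article*

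**What the plan says.** The Cost-effectiveness analysis section of the protocol article gives the cost model in one sentence: "Cost differences between groups will be estimated using regression analysis where all neck or back-related costs in a year are regressed on treatment". Treatment is the only regressor named.

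The same section describes two further analyses more loosely. For cost-effectiveness: "A cost-effectiveness analysis, using a mixed-model linear regression analysis, will be conducted to compare the interventions with home exercise (as the control"), with pain as the effect measure and no covariates listed. For cost-utility: "Finally, a cost-utility analysis comparing the intervention and control groups will be performed using the EuroQol-5D". The latter gives no model, QALY construction or covariates.

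The section on health care costs shows what is available at baseline. Utilization comes partly from "patient self-report questionnaires (baseline and weeks 4, 12, 26 and 52"). Of the EuroQol-5D it says: "It is measured at baseline and weeks 4, 12, 26, and 52". Indirect costs differ, with no baseline listed: "Indirect costs of wage and productivity loss are measured through patient self-report (weeks 4, 12, 26, and 52").

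For pain, the Treatment effect section states: "Baseline values will be used as covariates, and 95% confidence intervals will be placed on group differences". Allocation is described as follows: "Restricted randomization with a 1:1:1 allocation ratio has been applied using randomly permuted block sizes". No stratification factor is named.

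**The concern.** The article names baseline covariates for pain and, in the next subsection, writes the cost model without any, although a baseline measure of the same kind is collected. Prior use of care may predict later use. If it does, leaving it out keeps explainable variation in the residual, widens the interval for the cost difference, and leaves the estimate exposed to whatever imbalance in prior use arose by chance. The design as described does not balance the arms on utilization. The article's only power statement is for pain, so the precision of the cost comparison has no stated reserve.

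**Working it through.** **No cost figure to reproduce.** The article gives no sample size, power, SD or correlation for costs. Its one design figure, 88% power for an 8-point pain difference, comes without an SD and does not bear on this point.

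**Inputs.**
- Randomized per study: 240, so 240 / 3 = 80 per arm (Study population; Randomization).
- Loss to follow-up: 15% (Treatment effect). 240 × 0.85 = 204, so 204 / 3 = 68 per arm with one-year data.
- Within-arm correlation r between baseline utilization and one-year cost: not given. Assumed range 0.1 to 0.5.

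**Formulas**, for one baseline covariate with a common slope, in SD units of annual cost:
- Residual variance after adjustment = (1 - r²) × unadjusted variance, so the reduction is r².
- Unadjusted SE of a pairwise difference = √(2/68) = 0.171. Adjusted SE = 0.171 × √(1 - r²).
- Equivalent patients per arm = 68 / (1 - r²).
- A one-SE chance imbalance at baseline = √(2/80) = 0.158 SD. Its expected carry-over into the unadjusted cost difference = r × 0.158.

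| Assumed r | Variance reduction | Adjusted SE (SD units) | 68 per arm acts like | Carry-over of a one-SE imbalance (SD units) |
|---|---|---|---|---|
| 0.1 | 1% | 0.171 | 68.7 | 0.016 |
| 0.3 | 9% | 0.164 | 74.7 | 0.047 |
| 0.5 | 25% | 0.148 | 90.7 | 0.079 |

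Even at r = 0.5 the carry-over is 0.079 / 0.171 = 0.46 of the unadjusted standard error. Estimating the slope uses one of 204 - 3 = 201 residual degrees of freedom, about 0.5%, so at r = 0.1 the net gain is close to nothing.

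**Where r probably lies for costs.** Four features of the design point to a low value:
- The exclusion criteria remove people already under treatment for their spinal pain, which narrows the range of baseline provider use.
- Participants are asked not to seek other care during the 12 treatment weeks, which is 12 / 52 = 23% of the costed year.
- Indirect costs have no listed baseline, and utilization is only an indirect predictor of them.
- Manual visits, up to 20, are set by the treating chiropractor and enter direct costs. Their variation within the arm need not follow prior use.

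One feature points the other way: stable pain medication is allowed at entry, so medication use can vary at baseline and persist.

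**EuroQol-5D, for the recommendation only.** Suppose QALYs were the trapezoid area under the curve over weeks 0, 4, 12, 26 and 52, which the article does not say. The visit weights w are then 0.038, 0.115, 0.212, 0.385 and 0.250, with Σw² = 0.270. Assume equal variance and equal correlation c between all visits. The variance factor after adjusting for baseline is

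1 - [0.038 + 0.962c]² / [0.270 + 0.730c]

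which gives 0.78, 0.58 and 0.35 at c = 0.3, 0.5 and 0.7. These values show only that adjustment could matter more for utilities than for costs.

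**The case against.** The strongest reply is that a journal article condenses the plan. A sentence saying that costs are regressed on treatment names the regressor of interest and does not exclude others, and a covariate list is something an article may leave to the full protocol or analysis plan. This stands in part: the article does not forbid adjustment. It does, however, state the model instead of staying silent, and it names baseline covariates for pain just before. Asking for the cost model to be completed is therefore a comment on stated text.

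A second reply is that study treatment is a large part of cost and follows from allocation. Any part that is constant within an arm enters the treatment coefficient and does not dilute r. Only variation within an arm does, such as the number of manual visits. This limits the expected gain but does not remove it.

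A reader might be tempted to go further in three ways that the document does not support:
- **That the cost difference is biased or invalid.** Under 1:1:1 randomization the unadjusted difference is unbiased, and its standard error already reflects chance imbalance.
- **That the utility comparison is unadjusted.** The article gives no cost-utility model, so it neither adjusts for baseline EuroQol-5D nor rules this out.
- **That skewed costs will make the standard errors unreliable.** The article says only that regression will be used. It fixes neither the model form nor the way intervals are obtained.

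**Conclusion.** The point holds as a minor remark on efficiency. The stated cost regression names no baseline covariate although a relevant one is collected and the pain analysis adjusts for baseline. The cost is lost precision and conditional exposure to chance imbalance, with no loss of validity and no effect on the primary pain analysis.

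The size depends entirely on a correlation the article does not give. Over the assumed range of 0.1 to 0.5 the variance reduction is 1% to 25%, and the design features above make the lower part more plausible for costs. For the EuroQol-5D nothing is stated wrongly; adjustment there is a recommendation.

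**What to change.** Complete the cost sentence so that annual neck or back-related cost is regressed on treatment plus baseline utilization, with baseline pain as an optional further covariate. For consistency, state also that the EuroQol-5D or QALY difference is adjusted for baseline EuroQol-5D. If the full protocol or analysis plan already says this, a cross-reference is enough.

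The change costs a line or two of analysis wording. It needs no new data, visits or patients, and should be settled before cost results by arm are seen.

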In summary, on-going LBP and NP have substantial impact on the functional capacity and well-being of older people, in the absence of effective prevention and treatment strategies. We, therefore, designed two parallel multi-methods clinical studies focusing on elderly patients with non-acute LBP and NP. Each study includes a randomized clinical trial (RCT), a cost-effectiveness study alongside the RCT, and a qualitative study. The primary aims of the RCT are to determine the relative clinical effectiveness of 1) chiropractic manual therapy plus home exercise, 2) supervised rehabilitative exercises and home exercise, and 3) home exercise alone for LBP and NP patients 65 and older in both the short-term (12 weeks) and long-term (one year) using pain as the primary outcome measure. Secondary aims are to assess the short- and long-term relative effectiveness of the three interventions, using 1) patient-rated outcomes regarding back and neck disability, general health status, patient satisfaction, improvement, and medication use; 2) objective functional performance outcomes of spinal motion, trunk strength and endurance, and functional ability; and 3) cost-effectiveness and cost utility measures. Finally, the qualitative studies will describe LBP and NP patients' perceptions of treatment and the issues they consider when determining their satisfaction with care.

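### The cost-effectiveness and cost-utility analyses are planned only against the home-exercise control, although the stated aim covers all three interventions; no joint cost-effect contrast of manual treatment with supervised exercise is planned

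*Protocol article*

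**What the plan says.** The Cost-effectiveness analysis section of the protocol article has three components.

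- **Costs.** "A cost comparison of the intervention and control groups will be performed using data on direct and indirect costs". The next sentence adds: "Cost differences between groups will be estimated using regression analysis where all neck or back-related costs in a year are regressed on treatment".
- **Cost-effectiveness.** A mixed-model linear regression "will be conducted to compare the interventions with home exercise (as the control), using patient-rated pain as the effectiveness measure".
- **Cost-utility.** "a cost-utility analysis comparing the intervention and control groups will be performed using the EuroQol-5D".

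The aims are wider. In the Background section, "Secondary aims are to assess the short- and long-term relative effectiveness of the three interventions" opens a list whose third item is "cost-effectiveness and cost utility measures". The clinical analysis follows that wider aim: the Treatment effect section uses repeated measures ANCOVA "to measure differences between the 3 groups in patient-rated pain".

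**The concern.** The three 12-week programs are alternatives. Both active arms add something to the same home exercise program: one adds chiropractic manual treatment, the other adds supervised exercise sessions. A payer or patient willing to go beyond home exercise must then choose between the two additions. The cost-effectiveness sentence names only comparisons with home exercise. The cost-utility sentence names only intervention and control groups, without saying whether the active arms are kept separate or pooled. Under either reading, the choice between the active arms has no planned economic analysis that joins cost and effect.

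With three mutually exclusive options, the informative comparison is each option against the next less costly one that is not dominated. Two separate comparisons with a common control can both look favourable while one active arm is clearly the worse buy. The trial could then report that both active programs are acceptable value against home exercise, without saying which to prefer or what moving from one to the other costs.

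**Working it through.** No sample size, power or other stated figure depends on this point, so there is none to reproduce. The check has three parts.

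**1. Aim against planned contrasts**

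| Analysis | Contrast named | Manual vs supervised covered? |
|---|---|---|
| Aim (Background) | the three interventions | yes |
| Pain (Treatment effect) | differences among 3 groups | yes |
| Cost regression | differences between groups, costs regressed on treatment | possible, costs only |
| Cost-effectiveness (pain) | interventions vs home exercise | not named |
| Cost-utility (EuroQol-5D) | intervention vs control groups | not named; pooled or separate not stated |

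The gap is therefore confined to the last two rows.

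**2. Why comparisons with control alone may not suffice**

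The article gives no costs, utilities or expected effects, so every input here is assumed and shows only the mechanism. A and B are the two active arms in either order. Increments are against home exercise (C), with costs in arbitrary currency units and effects in QALYs.

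- Ratio against control = added cost / added effect.
- B against A = (cost of B − cost of A) / (effect of B − effect of A).

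| Case | A: cost, effect | B: cost, effect | A vs C | B vs C | B vs A |
|---|---|---|---|---|---|
| 1 | 400, 0.020 | 900, 0.030 | 20,000 | 30,000 | 500/0.010 = 50,000 |
| 2 | 400, 0.020 | 700, 0.024 | 20,000 | 29,167 | 300/0.004 = 75,000 |
| 3 | 800, 0.020 | 900, 0.030 | 40,000 | 30,000 | 100/0.010 = 10,000 |
| 4 | 600, 0.020 | 500, 0.030 | 30,000 | 16,667 | B cheaper and better |

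In cases 1 and 2 the ratio of B against control understates what the step from A to B costs. In case 3, A is extendedly dominated. In case 4, A is dominated outright, yet its ratio of 30,000 against control could pass as acceptable.

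Net benefit avoids this. Take case 2 at an assumed threshold of 50,000 per QALY:

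- A: 50,000 × 0.020 − 400 = 600.
- B: 50,000 × 0.024 − 700 = 500.

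A is preferred, although B's 29,167 against control lies below the threshold.

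**3. Can the data support the missing contrast?**

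The Randomization section states: "Restricted randomization with a 1:1:1 allocation ratio has been applied using randomly permuted block sizes". With 240 participants per study, that is 240/3 = 80 per arm. For an outcome with a common SD:

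- Active vs control: SE = SD × √(2/80) = 0.158 SD.
- Active vs active: SE = SD × √(2/80) = 0.158 SD.

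The precision is the same if the SDs are equal. The point estimate for B against A can be obtained by subtracting the two contrasts with control, but its standard error cannot be found from their two standard errors alone. Treating them as independent gives SD × √(4/80) = 0.224 SD, which is too large because both contrasts share the control arm (covariance SD²/80). The contrast should therefore come from one three-group model.

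**The case against.** Several points against the concern have force.

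- **Much of the comparison is already planned.** Pain differences across the three groups come with 95% confidence intervals, and the cost regression is not restricted to contrasts with control. A reader might infer that the choice between the active arms is never evaluated. The article does not support that: the separate cost and effect components are available or obtainable. What is missing is the contrast that joins them, with its uncertainty.
- **No ratio is named.** A reader might also infer that the plan will report two ratios against home exercise, and that these would be wrong by some factor. The article mentions no ratio and does not say how the mixed model combines costs with effects. If the model used net benefit with home exercise as the reference, the point estimates would rank all three arms correctly at a given threshold. The warning about ratios is therefore conditional.
- **Home exercise is a sensible comparator.** Both active programs build on it, and asking whether each addition is worth its cost is a coherent question. The planned contrasts are narrower than the aim in the Background section, but they do not flatly contradict it. The Abstract mentions the economic aims without naming a contrast.
- **An article condenses.** Rules for ranking arms and presenting uncertainty commonly sit in a fuller document, so their absence is no fault. The criticism rests on the comparator that the article does state.

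These points narrow the concern. They do not supply a planned cost-effectiveness or cost-utility contrast between the active arms.

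**Conclusion.** The concern holds in limited form. The stated comparators for cost-effectiveness and cost-utility are narrower than the three-way aim under which the article lists both analyses, and no joint contrast of manual treatment with supervised exercise is planned. If results are expressed as ratios against home exercise, they can make a dominated or poor-value active arm look acceptable. How large that effect would be here cannot be computed; the figures above are illustrations from assumed inputs. A reader might also expect the added contrast to be less precise than those with control. With 1:1:1 allocation and equal SDs it is about as precise, although precision may be limited for all of them. The point concerns a secondary aim and leaves the primary pain analysis untouched. It is worth correcting because the correction is cheap.

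**What to change.** In the Cost-effectiveness analysis section, define both the cost-effectiveness analysis (pain) and the cost-utility analysis (EuroQol-5D) as three-arm incremental comparisons, with the active arms kept separate:

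1. Order the three arms by observed mean cost.
2. Remove dominated and extendedly dominated arms.
3. Compare each remaining arm with the next.

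Equivalently, report net benefit for all three arms over a range of thresholds. Estimate the manual versus supervised exercise contrast and its uncertainty from the same three-group model as the contrasts with home exercise, which can stay in the report.

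The cost is a little extra analysis. The article already plans to collect health care use, pain and EuroQol-5D in every arm, so no new data or participants are needed. The downside is one more secondary contrast of limited precision, similar to that of the contrasts with control, whose interval should be shown.

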#### Qualitative analysis

Qualitative analysis of transcribed participant interviews will use an inductive approach toward content analysis, as a way of identifying themes and categories of responses [51-53]. Two investigators (MM and RE) will independently analyze the interviews and regularly meet to establish consensus on the coding of themes. Inter-rater reliability of text coding will be assessed, and kappa values of less than 0.8 will necessitate review of the coding structure. Categorized information from the transcribed interviews will be summarized and interpreted in the context of other study results. The frequency of themes will be quantified and representative patient quotations will be identified [53,54].

## Discussion

Low back pain (LBP) and neck pain (NP) are important health problems for both younger and geriatric individuals. Of particular concern is that conditions associated with LBP and NP, such as impaired strength and flexibility, can have very serious consequences for an older individual's independence and overall health. The best treatments for low back and neck conditions will not only aim to treat the pain specifically, but will also address associated strength and motion in a manner that enhances general function and improves quality of life. Chiropractic manual treatment and exercise are treatment approaches that aim to meet these needs and have demonstrated potential in younger individuals.

To our knowledge, these are the first randomized clinical trials to comprehensively address clinical effectiveness, cost-effectiveness, and patients' perceptions of commonly used treatments for elderly LBP and NP sufferers. This article presents the rationale and design of two mixed methods clinical trials, each consisting of an RCT, with cost-effectiveness and qualitative studies conducted alongside the central trial. Both are anticipated to be completed in 2007, at which time the results will be made available.
